### Hypotheses

Firstly, we hypothesised that compared to a waitlist control condition, parents receiving either form of the intervention will report the following short-term outcomes at 2-weeks post intervention:

a) Stronger beliefs and intention about engaging in self-care behaviour.

b) Higher levels of self-care behaviour.

c) Lower levels of fatigue and daytime dysfunction.

d) Lower levels of irritability, improved vigour and clarity of thought.

e) Improved sleep quality.

f) Lower levels of parenting stress and parenting hostility, and higher levels of parental warmth.

Secondly, we hypothesised that compared to a waitlist control condition, parents receiving either form of the intervention will report the following longer-term outcomes at 6-weeks post intervention:

a) Higher levels of parental self-efficacy.

b) Lower levels of depression, stress and anxiety.

c) Higher quality of the couple relationship and parent–child interactions.

Finally, we hypothesised that compared to the written information only condition, the intervention effects will be significantly stronger for parents in the written information with telephone support condition.

### Data analysis

A range of descriptive and multivariate data analyses will be used to assess the aims of the study. Descriptive statistics will be presented of the demographic characteristics of the sample. Means and standard deviations will be given for continuous outcomes, as well as medians and inter-quartile ranges where continuous data are skewed. Frequencies for categorical data will be reported. A mixed-design analysis of variance (split-plot ANOVA) will be conducted to compare the intervention and control conditions (between-subjects factor) on each of the primary and secondary outcomes at pre, post and follow-up (within-subjects factor). Effect sizes will be reported where appropriate, with 0.01, 0.06 and 0.14 as small, medium and large effect sizes for multivariate *η*^2^, while 0.2, 0.5 and 0.8 are small, medium, and large effect sizes for Cohen’s *d.* Finally, intention-to-treat analysis will be conducted using the last observation carried forward method for the missing post-intervention and follow-up data.

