### Sample size/power calculation

Power analysis using the program 'GPower 3.1.2' was conducted to determine the required sample size for the study. A 3-group comparative study would require a total sample of 184 participants (approximately 61 parents in each treatment condition) to have 80% power to detect a statistically significant finding at *p* < .05 and a moderate effect size for the short-term outcomes at two weeks post-intervention. Allowing for a 20% dropout rate, we aimed to recruit approximately 221 parents (approximately 74 participants in each treatment condition).

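### The three-wave split-plot ANOVA, unless gaps are imputed, leaves parents without a last form out of the test of the powered 2-week outcomes, and the plan does not say whether it or the separate LOCF intention-to-treat run is primary

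*Protocol article*

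**What the plan says.** Three parts of the protocol article bear on this point.

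- **Sample size/power calculation.** Power is set for "a moderate effect size for the short-term outcomes at two weeks post-intervention". The section then states: "Allowing for a 20% dropout rate, we aimed to recruit approximately 221 parents". The time point belongs to the effect size; the dropout rate has none.
- **Hypotheses.** Lower fatigue is listed among the 2-week outcomes.
- **Data analysis.** A split-plot ANOVA compares the arms "on each of the primary and secondary outcomes at pre, post and follow-up (within-subjects factor"), so there are three within-subject levels. After a passage on effect sizes the section closes: "Finally, intention-to-treat analysis will be conducted", with LOCF for missing scores at either follow-up. LOCF is the only missing-data method named. Neither analysis is called primary.

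**The concern.** A classical split-plot ANOVA needs a score at every within-subject level. Run on unfilled data, it removes a parent who returned the baseline and 2-week forms but not the last one, and that parent's observed 2-week score goes too. Entry to the test of the powered outcome then depends on something that happens later, after randomisation.

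Two things are at stake. The first is precision, because data already in hand go unused. The second is bias, if failure to return the last form is related to 2-week fatigue differently across arms. The protocol gives one reason why return might differ: under Waitlist control condition and Procedures, control parents are offered the programme only once their final questionnaire has arrived, whereas intervention parents already have it. The article gives no return rates, so this shows only that a difference is plausible.

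**Working it through.** **Inputs from the protocol.** Significance level .05 ("to detect a statistically significant finding at *p* < .05"; two-sided assumed); power 80% ("to have 80% power to detect"); three arms; 184 parents before dropout and 221 recruited; 20% dropout. The moderate effect has no number in the sample-size section. The Data analysis section gives d = 0.5 as medium ("0.2, 0.5 and 0.8 are small, medium, and large effect sizes for Cohen’s") and 0.06 as medium for eta-squared.

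**1. The plan's own figure.** It states: "would require a total sample of 184 participants (approximately 61 parents in each treatment condition").
- Pairwise comparison, d = 0.5, normal approximation: n = 2 × (1.960 + 0.842)² / 0.5² = 62.8, so 63 per arm and 189 in total. With 61 per arm, power is 78.9%. This is close to the plan's figure.
- One-way three-group F test: 158 in total at f = 0.25, and 154 at eta-squared 0.06.

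The pairwise reading is the nearer, so I use it below, with the F test as a check.

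**2. If the 20% is total loss by the last form.** Complete cases: 221 × 0.80 = 176.8, about 177. Parents with a 2-week score number between 177 and 221, so the unfilled ANOVA leaves out between 0 and 44 observed 2-week scores. Complete cases are close to the planned 184, so planned power is roughly preserved.

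**3. If the 20% is loss by 2 weeks.** Per arm, 221 / 3 × 0.80 = 58.9 parents have a 2-week score. Assume a further 5%, 10% or 15% of these miss the last form. Power is for a two-sided t-test with 2n − 2 degrees of freedom and non-centrality 0.5 × √(n/2).

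| Further loss (assumed) | n per arm | Total used | 2-week scores left out | Power, one arm v control |
|---|---|---|---|---|
| 0% | 58.9 | 177 | 0 | 76.8% |
| 5% | 56.0 | 168 | 9 | 74.6% |
| 10% | 53.0 | 159 | 18 | 72.3% |
| 15% | 50.1 | 150 | 27 | 69.8% |

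Check with the three-group F test at eta-squared 0.06: power is 84%, 81% and 79% at 168, 159 and 150. All of these are single-time-point approximations to the three-wave model.

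**4. Bias in the 2-week contrast.** Take the 2-week fatigue score as standard normal within arm, and let the log odds of missing the last form rise linearly with it. The shift is the mean score among parents kept.
- 15% missing, odds ratio 1.5 per SD: −0.060 SD. Odds ratio 2 per SD: −0.098 SD.
- 10% missing, same odds ratios: −0.040 and −0.066 SD.

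The bias is the difference between arms:
- fatigue-related loss in a WAP arm only, 15%: 0.06 to 0.10 SD in favour of WAP;
- same slope in both arms, 15% v 10% loss: 0.060 − 0.040 = 0.02, and 0.098 − 0.066 = 0.03 SD;
- same slope and same loss in both arms: about 0.

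Every rate and odds ratio in this step is an assumption.

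**5. What the LOCF run does.** Parents were randomised only after the baseline questionnaire came back, so LOCF can fill all three waves for anyone with a baseline score. An observed 2-week score is kept. A missing 2-week score becomes the baseline value, and a missing last score becomes the latest earlier one.

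**The case against.** A reader might infer that the main result is a completers' comparison, that intention-to-treat is an afterthought, and that observed 2-week scores are thrown away. The protocol does not establish any of this. It does not restrict the ANOVA to parents with all forms, does not call it the main result, and does not call the intention-to-treat run supplementary. The word that opens the closing sentence also introduces the third formal hypothesis, so it may only order the text. LOCF may simply be how the same ANOVA is run, in which case the 2-week scores are kept. This objection stands. What remains is that a separately announced intention-to-treat analysis, with missing data mentioned only there, most naturally implies that the preceding ANOVA is something else.

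It is also tempting to say that the dropout allowance covers the 2-week outcomes alone. It does not say so, and the power losses in step 3 arise only under that assumption.

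The numbers are fragile. The F test gives smaller stakes, and the larger bias needs fatigue-related loss in one arm and none in the other. The starting 77% partly reflects 221 = 184 × 1.2, which leaves 177 after 20% loss and is a separate matter.

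Last, an article may leave the analysis set to a statistical analysis plan. That is fair for what it omits. But this article does fix the model, its three time levels and the missing-data method, and the point concerns those choices.

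**Conclusion.** The point holds in a limited form. The plan announces two analyses without ranking them, and neither handles the powered 2-week outcomes well. On unfilled data, the ANOVA makes the 2-week test depend on return of a later form. The LOCF run keeps observed 2-week scores but substitutes earlier ones for those missing.

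If the 20% dropout is total loss by the last form, about 177 complete cases remain and the cost is mainly selection and unused data, up to 44 scores. If it is loss by 2 weeks, pairwise power at d = 0.5 falls from about 77% to 75–70% under an assumed further 5% to 15% loss. Bias lies between about 0 and 0.06–0.10 SD, the upper end being at most one fifth of d = 0.5 (0.10 / 0.5). That upper end rests on one-sided selection for which the protocol gives no data. The case for change does not depend on these figures: on either reading, a method that uses all observed scores is better than the one stated.

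**What to change.** In the Data analysis section, name as primary one analysis of all randomised parents by allocated arm that uses every observed score. Two forms would serve:

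- a likelihood-based mixed model on all waves, with contrasts at 2 weeks and at 6 weeks; or
- baseline-adjusted ANCOVA at each time point, including every parent with a score at that time.

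Label the ANOVA on parents with all three forms and the LOCF run as sensitivity analyses. State also which time point the 20% dropout refers to.

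The cost is a few sentences and slightly different code. No new data and no more parents are needed. The Background section says that data collection is still under way, so the change can be made before analysis.
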